### Statistical analysis

The statistical analysis will be conducted using SPSS 28.0 software. Qualitative data will be represented in percentages or proportions, and quantitative data with a normal distribution will be presented as the mean ± standard deviation, while non-normally distributed data will be expressed as the median and interquartile range. When analyzing variables measured at multiple time points, a repeated measures analysis of variance (ANOVA) will be used. To correct for multiple comparisons, Bonferroni correction will be applied. Effect sizes and 95% confidence intervals (CI) will also be calculated. Analysis of other variables will include independent t-tests or Wilcoxon rank-sum tests, chi-square test or Fisher’s exact tests. The Intention-to-Treat (ITT) principle will be applied to assess baseline characteristics and primary and secondary outcomes. For participants who drop out of the study, missing data will be addressed using multiple imputations by chained equations (MICE), provided the missingness is determined to be missing at random (MAR). This approach aims to ensure the robustness of the analysis and minimize potential biases introduced by missing data. All adverse events (AEs) will be compared between groups using the chi-square test or Fisher’s exact test. A two-sided test will be utilized, with a significance level *p*-value set at 0.05.

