## Abstract

**Background:**

Primary dysmenorrhea (PD) is a common gynecological disorder that significantly affects women’s work and personal lives, especially in acute episodes when immediate pain relief is often needed. The objective of this study is to evaluate the immediate analgesic effect of acupuncture for acute PD within 10 min.

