### Secondary outcomes

The secondary outcomes include the effective rate at various time points (0, 0–1, 2, 4, 6, 8 min), VAS pain score, blinding assessment (assessed by asking participants whether they received true acupuncture and their confidence in this response), and treatment effectiveness expectations scale.

The VAS is one of the most commonly used pain intensity assessment tools (Table 2) (29). The scale consists of a 10 cm horizontal line, with one end labeled as ‘0’ to indicate ‘no pain at all’ and the other end labeled as ‘10’ to represent ‘the worst imaginable pain.’ The line presented to participants only displays the two anchor points (‘0’ and ‘10’) without any intermediate numerical markings. Participants will be instructed to mark a position on the line using a pen (e.g., with a dot or an ‘x’) that best represents their current pain intensity at that moment. The VAS will be assessed seven times in total, including at baseline, 0–1 min (during treatment), 2 min (during treatment), 4 min (during treatment), 6 min (during treatment), 8 min (during treatment), and 10 min (at the end of treatment).

After the participants make their mark, the scale will be collected by trained study personnel, who will measure the distance (in millimeters) from the ‘0’ anchor to the marked point using a ruler. This process allows for precise scoring, including fractional scores (e.g., 5.5), based on the exact position of the mark.

Currently, there are no studies specifically targeting the immediate analgesic response in primary dysmenorrhea to determine the minimum clinically important difference (MCID) threshold. Therefore, we combined previous clinical experience and previous studies in acute pain patients, where a decrease of approximately 10–13 mm on the visual analog scale (VAS) can be considered the minimum clinically important difference (MCID) (30).

To ensure uniformity, participants will receive standardized verbal instructions, emphasizing that the marking should reflect their perception of pain without additional guidance or interference. The measurement will be conducted in a quiet and private setting to minimize distractions and ensure accuracy. Study personnel will systematically record the scores to maintain consistency and data integrity.

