### Sample size

Based on previous study (31) and our past clinical treatment experience, we anticipate that after 10 min of acupuncture treatment, the mean change in VAS score in the acupuncture group will be 4.21 (SD = 1.0), whereas the mean change in VAS score in the sham acupuncture group will be 2.15 (SD = 1.0). With *α* = 0.025 (unilateral, significance level), *β* = 0.1 (type II error rate, or power = 90%), *Δ* = 1.3 (minimum clinically important difference, this is equivalent to a difference of 13 mm on the visual analog scale, which represents the minimum clinically significant change in acute pain.), and 
k
=1 (allocation ratio) (30). The sample size was calculated based on the following formula:

$$n_{C}=\frac{{\left(Z_{1-\alpha }+Z_{1-\beta }\right)}^{2}\sigma^{2}{\left(1+\frac{1}{k}\right)}^{2}}{{\left(\mu_{T}-\mu_{C}-\Delta \right)}^{2}}$$

$\mu_{T}$
: trial group mean; 
$\mu_{C}:$
 control group mean; 
σ
: standard deviation (assuming equal standard deviations for both groups).

Based on the calculations, each group will require at least 36 participants (32). Taking into account an 8% dropout rate, the adjusted sample size will be 40 participants per group. Therefore, we plan to recruit at least 80 participants for this study.

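### Plain Bonferroni is valid but needlessly conservative for the correlated earlier readings (secondary outcomes); Holm over the same family keeps the same error control and never rejects less

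*Protocol article*

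**What the plan says.** All of the following is from the Protocol article.

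- **Objective** (Abstract, Background): "The objective of this study is to evaluate the immediate analgesic effect of acupuncture for acute PD within 10 min".
- **Primary outcome:** the proportion whose VAS falls by at least 50% from baseline, at 10 min.
- **Secondary outcomes:** "The secondary outcomes include the effective rate at various time points". The abstract lists 0-1, 2, 4, 6 and 8 min; the Secondary outcomes section also lists 0. VAS itself is a further secondary outcome at these times.
- **Statistical analysis:** "When analyzing variables measured at multiple time points, a repeated measures analysis of variance (ANOVA) will be used". The next sentence is the multiplicity rule, "To correct for multiple comparisons, Bonferroni correction will be applied". Effect sizes with 95% CIs follow, then chi-square or Fisher tests for other variables. The general level is two-sided 0.05 ("A two-sided test will be utilized, with a significance level").

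The document does not say which comparisons Bonferroni covers, how many there are, or whether the 10-min comparison is among them. No stepwise, ordered or gatekeeping procedure is described.

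**The concern.** The earlier readings come from the same participants two minutes apart or less, so their test statistics will be strongly correlated. Bonferroni guards against the worst case of dependence and holds every comparison to the same strict threshold, however many others have already been rejected. If the family is the five earlier between-group comparisons, that threshold is 0.05/5 = 0.01 at each reading.

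At stake is how often a real difference at an earlier reading is formally declared in a small trial about speed of relief. A procedure with identical error guarantees and a more generous rule is available at no cost in data, so the lost power buys nothing.

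**Working it through.** **1. The plan's own figure.** Sample size section: mean VAS change 4.21 against 2.15, common SD 1.0, margin 1.3, one-sided alpha 0.025, power 90%. With the usual two-sample factor (1 + 1/k) = 2:

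n = (1.960 + 1.282)² × 1.0² × 2 / (4.21 − 2.15 − 1.3)² = 10.51 × 2 / 0.76² = 21.01 / 0.5776 = 36.4.

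The stated 36 is reproduced to within rounding, and 36 / 0.92 = 39.1, rounded up to 40 per arm. (As printed, the formula squares (1 + 1/k) and would give about 73. That is a separate matter.)

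**2. What Bonferroni costs at one reading.** Exact enumeration of the two-sided chi-square test, 40 per arm, with assumed response rates:

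| Response rates | Power at 0.05 | Power at 0.01 |
|---|---|---|
| 60% vs 30% | 79.6% | 55.4% |
| 30% vs 10% | 63.2% | 38.5% |

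The gap is the most that any step-down rule could recover at that reading, because no step-down threshold exceeds 0.05.

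**3. Why Holm cannot do worse.** Order the p-values of m comparisons and test the j-th smallest at 0.05/(m − j + 1), stopping at the first failure. For m = 5 the thresholds are 0.05/5 = 0.010, 0.05/4 = 0.0125, 0.05/3 = 0.0167, 0.05/2 = 0.025 and 0.05. None is below Bonferroni's 0.010, so every p-value at or below 0.010 is still rejected. Like Bonferroni, Holm needs no assumption about correlation.

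**4. Size of the gain.** The table gives the chance of declaring a responder difference, in per cent. All runs use the planned 10-min means and SD. The assumptions not in the documents are:
- Run A: 40 per arm, baseline VAS uniform on 4-9, correlation 0.8 between readings 2 min apart.
- Run B: 40 per arm, correlation 0.8.
- Run C: 36 per arm, baseline mean 6.5 (SD 1.2, limited to 4-9), autoregressive correlation 0.8. Holm was gated on the 10-min test, which passed about 100% of the time in these rows.

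| Run | Assumed course, reading | Bonferroni over 5 | Holm | Holm gain | Backward sequence |
|---|---|---|---|---|---|
| A | linear, 6 min | 67 | 71 | 4 | 89 |
| A | square root, 4 min | 77 | 83 | 6 | 93 |
| A | square root, 2 min | 4 | 19 | 15 | 36 |
| B | linear, 6 min | 59 | 62 | 3 | 82 |
| B | square root, 4 min | 69 | 75 | 6 | not quoted |
| B | square root, 2 min | 12 | 27 | 15 | not quoted |
| C | linear, 6 min | 50.8 | 55.7 | 4.9 | 79.5 |
| C | linear, 8 min | 96.5 | 96.6 | 0.1 | 99.4 |
| C | fast rise then plateau, 4 min | 69.5 | 79.8 | 10.3 | 92.7 |

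With a smaller effect (3.5 vs 2.15, SD 1.5; run A's other assumptions), power at 8 min was 40-48% with Bonferroni and 40-51% with Holm.

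**5. The ordered alternative when the effect does not last.** The backward sequence (10, 8, 6, 4, 2, 0-1 min, each at two-sided 0.05) held family-wise error at 0.049-0.051 in every null pattern tried. Its power advantage depends on the time course:
- Effect peaking at 6 min and halving by 10 min (run B): 58% against 96-100% for Bonferroni at 4-6 min.
- VAS with a dip at 6 min (36 per arm): at 4 min, sequence 26%, Bonferroni 80%, gated Holm 83%.
- Responders, effect peaking at 4-6 min and falling to half by 10 min (run C): at 4 min, sequence 80.6%, gated Holm 80.6%, gated Bonferroni 79.8%, ungated Bonferroni 96.7%. Here the gate on 10 min causes the loss. With the same gating, Holm is still not below Bonferroni.

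**The case against.** **The family is inferred.** The Bonferroni sentence follows the repeated measures ANOVA sentence directly, and the tests suited to binary outcomes come later. It may be meant for the VAS comparisons only. This stands: a reader might infer that the plan tests five responder rates at 0.01 each, but the document states neither that family nor that threshold. The percentages above describe one plausible family. The algebra in step 3 does not depend on this, since Holm is at least as powerful whichever family is meant.

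**No onset time is planned.** A reader might infer that Bonferroni will make the trial report too late an onset. The document names no onset endpoint and no rule for deriving one, and it commits to effect sizes and 95% CIs, so earlier differences would not be reported only as significant or absent.

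**The fixed sequence is not simply better.** A reader might infer that testing backwards from 10 min should replace Bonferroni outright. That needs an effect that neither fades nor dips before 10 min. The Introduction expects the peak between 5 and 10 min, which leaves room for a decline by 10 min, and step 5 shows how large the loss can then be.

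**Bonferroni is valid and standard.** This is also true. The point concerns efficiency on supportive outcomes and shows no inflated error or false statement. What remains is that Holm gives the same guarantee under the same assumptions and never rejects less.

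**Conclusion.** The concern holds as an efficiency point. Plain Bonferroni controls error correctly but is needlessly conservative for the correlated earlier readings. Holm over the same family is a near-free improvement: its dominance over Bonferroni is a mathematical fact. The size of the gain, about 0 to 15 percentage points at marginal readings, rests on assumed onset curves, correlations and baseline VAS, and on a family of five. Where power is already near 100% or near zero the gain is negligible; for responders at 0-1 min neither rule has useful power.

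The fixed sequence adds about 10 to 30 points if the effect builds or plateaus to 10 min and can lose more than that if it wanes, so it is a trade-off for the sponsor to judge. Nothing here bears on the 10-min primary outcome or its stated power.

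**What to change.** Under Statistical analysis, replace the Bonferroni sentence with Holm's step-down procedure at a two-sided family-wise level of 0.05. Name the family in the same sentence, for example the five between-group comparisons at 0-1, 2, 4, 6 and 8 min, with the 10-min primary outside it. Keep the estimates and 95% CIs at every time.

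If the sponsor expects an effect that does not fade or dip before 10 min, a fixed sequence may be specified instead: once the 10-min primary is significant, test 8, 6, 4, 2 and 0-1 min in that order, each at two-sided 0.05, stopping at the first non-significant result. The text should state that expectation and acknowledge that a non-significant later reading blocks formal claims at earlier ones.

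The cost is one sentence, fixed before unblinding, with no extra data or participants. The small downside of Holm is that it has no equally simple matching simultaneous confidence intervals.

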### Sham acupuncture group

For participants in the SA group, PSD and blunt needle will be used. During the procedure, the acupuncturist will have blunt needles touching the skin without penetrating the surface, the participants will feel a slight tingling sensation. The rest of the operation is the same as the Acupuncture group.

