### Adverse events reporting and safety monitoring

Throughout the entire research process, participants undergoing acupuncture treatment may experience AEs such as increased pain instead of relief, subcutaneous congestion or hematoma, or even fainting or other severe incidents. Whether these adverse events are directly related to the treatment in this study or not, we will promptly and appropriately address them. In the event of an AE, the participant will receive immediate clinical assessment and necessary medical care. For mild AEs (e.g., minor bruising or needling discomfort), local symptomatic treatment will be provided. For moderate or severe AEs (e.g., vasovagal syncope, severe pain), the intervention will be paused or terminated immediately, and the participant will be closely monitored by qualified medical staff until full recovery. Emergency procedures will be in place to ensure patient safety at all times. Detailed records of all AEs will be documented in CRFs, and a comprehensive report will be submitted to the Ethics Committee of The Second Affiliated Hospital of Yunnan University of Chinese Medicine.

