For this study, a commonly utilized placebo technique involving the use of blunt non-penetrating needle stimulation is chosen as the control intervention (39, 40). To mitigate potential bias arising from unblinding, acupuncturists are instructed to maintain minimal contact between the blunt needle and the acupoints, thereby inducing only a slight sensation of pricking to minimize variations in needle perception. Furthermore, a blinded assessment scale will be developed to evaluate the efficacy of the blinding methodology. For the study time, the general drug onset time is 15 min (9), while some studies have shown that the onset time of acupuncture and SA is 10 min (41); to better validate the immediate analgesic efficacy of acupuncture, the study is set up for 10 min. And the treatment duration is short, at the end of the treatment, when acupuncture could not provide enough pain relief, we could use traditional medicines in time. The use of emergency analgesics is counted in both groups and the remedial analgesia rate is calculated.

The VAS is a commonly used scale for the clinical evaluation of pain and provides a simple, intuitive, continuous, and sensitive way to quantify the subjective perception of pain for PD assessment. The objective of this randomized controlled study is to investigate the immediate analgesic effect of acupuncture within 10 min in treating acute PD, by comparing the outcomes between the Acupuncture group and the SA group. The findings will not only clarify the efficacy of acupuncture as a fast-acting, low-risk, non-pharmacologic intervention but also provide evidence-based support for its integration into clinical practice. Specifically, the results may inform clinical decision-making and promote the use of acupuncture as a front-line treatment strategy in emergency or first-contact care settings, such as gynecological outpatient clinics, urgent care units, or primary health centers, particularly for patients for whom pharmacological treatments are unsuitable or who have concerns about them.

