Despite efforts to improve the validity of this study, there are some limitations. Firstly, the lack of a positive control group prevents direct comparisons between acupuncture and other therapies. Second, the single-centre design may limit the generalisability of the results, and multi-centre validation is needed. Third, in this study, sham needles are blunt-tipped and touch the skin without penetration, a commonly used control method. Nevertheless, skin contact may still induce physiological responses, so residual non-specific effects cannot be fully excluded. This is a potential limitation of our sham needle design and should be considered when interpreting the study results. Finally, Although the focus of this study is to assess the immediate analgesic effects of acupuncture on patients with acute primary dysmenorrhea, the lack of short-term or delayed follow-up observations limited the interpretation of the intervention’s sustained and cumulative analgesic effects. Future studies will conduct follow-ups over a longer observation period to explore whether the analgesic effects of acupuncture can persist beyond immediate treatment and further clarify its potential cumulative effects.

In short, PD patients are in urgent need of rapid pain relief. Although acupuncture is considered an effective treatment, there is a lack of research evidence to support it. Therefore, the results of this study will provide an easy and rapid treatment option for PD patients. Importantly, the results may help reduce reliance on NSAIDs by providing a safe and immediately effective non-pharmacological alternative.

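### The only stated adverse-event inference is a test against non-penetrating sham with 40 per arm, which says little about the low-risk and safe wording in the Discussion

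*Protocol article*

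**What the plan says.** **Analysis of harms.** Protocol article, Statistical analysis: "All adverse events (AEs) will be compared between groups using the chi-square test" or Fisher's exact test. The same section closes with "A two-sided test will be utilized, with a significance level" set at 0.05. It also plans percentages or proportions for qualitative data. A general sentence promises effect sizes and 95% confidence intervals; it comes after the repeated-measures and Bonferroni text and names no outcome.

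**Size.** Under Sample size, "the adjusted sample size will be 40 participants per group". The calculation uses VAS change only. The protocol gives no adverse-event rate, tolerable limit or safety margin.

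**Comparator and expected harms.** In the sham arm the acupuncturist will have "blunt needles touching the skin without penetrating the surface", whereas the Acupuncture group section describes needles inserted 20 to 30 mm. The adverse-event section lists increased pain, "subcutaneous congestion or hematoma, or even fainting or other severe incidents".

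**Anticipated message.** In the Discussion the findings are to "clarify the efficacy of acupuncture as a fast-acting, low-risk, non-pharmacologic intervention". The closing paragraph says the results may reduce reliance on NSAIDs by "providing a safe and immediately effective non-pharmacological alternative". The limitations paragraph concedes that, without a positive control, acupuncture cannot be compared directly with other therapies.

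**The concern.** A stated analysis and an anticipated conclusion do not fit together. Because the sham does not break the skin, a harm such as hematoma should arise almost only in the acupuncture arm. For such harms the useful question is how high that arm's rate could be. A test of no difference from sham does not answer it, and at this size a non-significant result is likely even when needling causes harm at a rate that would matter.

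The practical risk lies in reporting. A finding of no significant difference in adverse events could appear beside the safe and low-risk wording and be taken as support for it, although the data would still be compatible with a sizeable harm rate.

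**Working it through.** **1. Where 40 per arm comes from.** Inputs from Sample size: mean changes 4.21 and 2.15, SD 1.0, Δ = 1.3, one-sided α = 0.025, power 90%, 1:1 allocation, 8% dropout.
- Net difference: 4.21 − 2.15 − 1.3 = 0.76.
- Standard formula: n = (z₀.₉₇₅ + z₀.₉₀)² × σ² × (1 + 1/k) / 0.76² = 36.4 per group, which the protocol gives as 36.
- Dropout: 36 / 0.92 = 39.1, rounded up to 40.

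The figure of 40 is therefore reproduced, and no harm rate enters it. (The formula as printed squares the allocation factor and would give 72.8; that is a separate matter.)

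**2. How many events the test needs when sham has none.** For a events of 40 against 0 of 40:
- Fisher, two-sided (equal arms): p = 2 × C(40,a) / C(80,a)
- Uncorrected chi-square: χ² = 80a / (80 − a), compared with 3.84

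| Events, acupuncture vs sham | Fisher p | Uncorrected chi-square p |
|---|---|---|
| 3 vs 0 | 0.241 | 0.077 |
| 4 vs 0 | 0.116 | 0.040 |
| 5 vs 0 | 0.055 | 0.021 |
| 6 vs 0 | 0.026 | 0.011 |

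Fisher needs at least 6/40 (15%) and the uncorrected chi-square at least 4/40 (10%).

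**3. Probability of missing a true difference.** The rates are assumptions, because the protocol gives none. At 10% vs 0%:
- Fisher: P(X ≥ 6 | 40, 0.10) = 0.206, so the miss rate is 79.4%.
- Uncorrected chi-square: P(X ≥ 4 | 40, 0.10) = 0.577, so the miss rate is 42.3%.
- Yates-corrected chi-square: same as Fisher, 79.4%.

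Exact enumeration over all tables, 40 per arm unless stated:

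| Assumed true rates, acupuncture vs sham | Fisher misses | Uncorrected chi-square misses |
|---|---|---|
| 5% vs 0% | 98.6% | 86.2% |
| 10% vs 0% | 79.4% | 42.3% |
| 15% vs 0% | 43.3% | 13.0% |
| 20% vs 0% | 16.1% | 2.8% |
| 10% vs 1% | 85.0% | 55.6% |
| 10% vs 5% | 95.7% | 85.4% |
| 10% vs 0%, 36 per arm | 85.5% | 50.9% |

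At 10% vs 0% the expected event count is (4 + 0)/80 × 40 = 2 per arm. Fisher is the conventional choice at such counts, so its column is the more likely one to apply.

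**4. What the acupuncture arm alone would show.** Exact (Clopper-Pearson) two-sided 95% limits:
- 0/40: upper limit 1 − 0.025^(1/40) = 8.8%
- 1/40: upper limit 13.2%
- 4/40: 2.8% to 23.7%
- 5/40: upper limit 26.8%

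So 5/40 against 0/40 is not significant by Fisher, yet the acupuncture rate could be as high as about 27%.

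**The case against.** A reader might infer that the protocol treats a non-significant adverse-event test as proof of safety. It does not say so. Where the authors use a rule of that kind they write it out: under Secondary outcomes, blinding counts as successful if correct guesses do not significantly exceed half. No such rule is attached to adverse events.

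A reader might also infer that the safety wording rests on the p-value alone. That is too strong as well. Percentages are planned, the sentence on effect sizes and intervals is not restricted to any outcome, all adverse events are recorded and reported to the Ethics Committee, and a data monitoring committee is foreseen. The last two are oversight rather than inference, but the first two could yield most of what is wanted.

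Further points on the other side:
- Safety is neither the stated objective nor a listed primary or secondary outcome, and low power for harms is normal in a small efficacy trial. This stands; the sample size is not the complaint.
- The low-risk and safe phrases are discussion wording, and the NSAID sentence is hedged. This stands in part. Both sentences nevertheless concern what this trial's results will show.
- The choice of interval method is often left to an analysis plan that is not shown. This stands for the detail. The mismatch between the stated analysis and the anticipated message is visible in the article itself.
- The 79% depends on the test and on assumed rates, and increased pain can also occur under sham. This stands, so both tests are shown. At a true 10%, sham events make detection harder, not easier.

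**Conclusion.** The point holds in limited form. The one inference the protocol ties to adverse events is a two-sided 0.05 test against a non-penetrating sham, and with 40 per arm it carries little information about safety. Under assumed rates of 10% vs 0%, the difference is missed about 79% of the time by Fisher (or Yates-corrected chi-square) and about 42% by the uncorrected chi-square. At 5% vs 0% both miss it more than 85% of the time. Even an event-free acupuncture arm excludes only rates above 8.8%.

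The documents do not support reading this as a prespecified rule that non-significance means safety, as an error in trial size, or as a claimed comparison with NSAIDs, which the limitations paragraph already rules out. What remains is a gap between the analysis stated for harms and the conclusion the Discussion anticipates.

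**What to change.** In Statistical analysis:
- Keep the chi-square or Fisher comparison, labelled as descriptive.
- Add, for each arm, the incidence of any adverse event and of each type with exact (Clopper-Pearson) 95% confidence intervals, and the between-arm risk difference with its 95% confidence interval.
- State that a non-significant comparison will not be taken as evidence of safety.

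In the Discussion, limit low-risk and safe to what the upper confidence limit in the acupuncture arm supports (with 0/40, for example, that only rates above about 9% are excluded). Keep the wording consistent with the stated lack of a positive control.

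The cost is a few sentences. No extra participants, data or procedures are needed. The drawback is a less favourable safety statement.
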